## Materials and Methods

### Study Design

This study is designed as a randomized, double-blind, placebo-controlled multicenter clinical trial in accordance with the Helsinki Declaration. This trial is planned to test the hypothesis that TangWang prescription can delay in the progression of DR. A total of 384 participants will be randomly divided into two groups, which will both be administered basic treatments, consisting of oral calcium dobesilate capsules (Ebewe Pharma Ges.m.b.H.Nfg KG, 0.5 g three times per day). All the participants will be randomly assigned to either the treatment group or the control group. The study group will be received the intervention with oral calcium dobesilate capsules + TangWang prescription (one bag twice a day). And the control group will be received the intervention with oral calcium dobesilate capsules + the placebo (one bag twice a day) (Sichuan New Green Pharmaceutical Technology Development Co., Ltd.). Furthermore, diabetes education and diet, as well as rational control of blood glucose, lipids, and pressure will be performed in the two groups according to the American Diabetes Association guidelines.

The central randomization system uses a randomly permuted block design, which includes subject screening, randomization, emergency exposure of blindness, designated drug, drug supply, and other functions. The treatment duration is set at 48 weeks, and the study medications will be labeled by pharmacists according to the randomized list prepared by the central randomization system. The trial schematic flow is illustrated in Figure 1.

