### Sample Size Calculation

According to preliminary research data (Lian et al., 2015), the rate of retinal microvascular disease was reduced by 3.6% in the placebo group, and we predicted that the rate of retinal microvascular disease would be reduced by 8.9% in the TangWang prescription group. Therefore, the sample content formula was estimated using two overall rate hypothesis tests: Assuming that α = 0.05 and β = 0.10 according to the one-sided test, to obtain the tabular value, uα = 1.64485 and uβ = 0.84162, the data will be placed in the formula to obtain an n = 166.82. Therefore, each group needs 167 participants and considering a drop-out rate of no more than 15%, and each group would need 192 participants, for a total of 384 participants.

Furthermore, the rate of retinal microaneurysms disease increased by 3.6% in the placebo group, and according to the above formula, we would need n = 108.78 patients. Therefore, each group requires 109 participants, and if we assume a drop-out rate of no more than 20%, each group needs 132 participants for a total of 264 participants. Based on these two conclusions, 384 participants will be included in this study.

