We hypothesize that the patients with DR will benefit from TangWang prescription. If successful, this study will provide evidence that the TangWang prescription delays in the progression of DR. Although this protocol uses a rigorous randomized controlled trial to evaluate the effectiveness of the drug, there might also be potential limitations for this study. Firstly, in this multicenter trial, measurement errors in laboratory tests are also inevitable due to different medical equipment in several research centers. Secondly, there might be several individual differences in the subjects, possibly leading to different efficacy of the drug. Thirdly, the long treatment period and tight glucose control may lead to poor patient compliance, which might greatly influence the therapeutic effect. These questions should be explored more thoroughly in the future studies.

DR seriously threatens the vision of working-age people. For patients with NPDR, early treatment is of great significance. In recent years, the prevention and treatment of diabetic retinopathy by Chinese medicine has been a hot research topic. Up to date, this is the largest randomized controlled trial of Chinese medicine for diabetic retinopathy. In this protocol, a double-blind, randomized, placebo-controlled trial will be strictly implemented in multiple research centers. As the gold standard for evaluating drug efficacy, the implementation of the RCT will obtain high-level evidence-based medical evidence, which would fill up the gap in the treatment of early diabetic retinopathy.

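### The worsening sample size (n = 108.78) comes from a two-proportion formula missing a factor 2 and silently assumes 0% worsening on TWP; the same formula error sets the 384

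*Protocol article*

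**What the plan says.** The Sample Size Calculation section of the protocol article contains two calculations.

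- **Improvement.** It takes it that "the rate of retinal microvascular disease was reduced by 3.6% in the placebo group" and predicts that "the rate of retinal microvascular disease would be reduced by 8.9% in the TangWang prescription group". With a one-sided α of 0.05, a printed β of 0.10, uα = 1.64485 and uβ = 0.84162, it reports n = 166.82, hence 167 per group. This is raised to 192 per group for 15% drop-out.
- **Worsening.** It says that the rate "increased by 3.6% in the placebo group, and according to the above formula, we would need n = 108.78 patients". This is rounded to 109 per group and raised to 132 per group (264 in total) for 20% drop-out. No TWP worsening rate is printed, and neither is the formula.

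The section ends: "Based on these two conclusions, 384 participants will be included in this study".

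Study Design gives the aim: "This trial is planned to test the hypothesis that TangWang prescription can delay in the progression of DR". The Discussion says that, if successful, "this study will provide evidence that the TangWang prescription delays in the progression of DR". Under Primary Outcome, each patient is classed as aggravated, unchanged or reduced. Under Statistical Analysis, the groups are compared by a chi-square test, and all tests are two-sided at 0.05.

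**The concern.** The worsening calculation is the only one that bears directly on the stated hypothesis of delayed progression. It cannot be checked as printed because one of its two rates is missing. Its result also looks too small: 109 per group to detect any reduction from a rate as low as 3.6%, where 192 placebo patients would yield about 7 events (192 × 0.036 = 6.9).

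The closing sentence of the section relies on it. A reader is led to think that 264 patients are enough for progression and that 384 leaves a margin. If that is wrong, the trial may have little chance of showing less worsening. A positive primary test driven by improvement could then be reported as delay.

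**Working it through.** **Inputs.** From Sample Size Calculation: worsening on placebo 3.6%; improvement 3.6% vs 8.9%; uα = 1.64485; uβ = 0.84162; drop-out 20% and 15%. From Statistical Analysis: two-sided 0.05, chi-square. The percentages are read as proportions of patients who worsen or improve. The printed uβ is the quantile for 80% power, although β is printed as 0.10. The printed quantile is used below.

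**1. Reproducing the printed figures.** Write p̄ = (p₁ + p₂)/2 and q = 1 − p. The standard pooled formula is

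n = [uα·√(2p̄q̄) + uβ·√(p₁q₁ + p₂q₂)]² / (p₁ − p₂)².

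It does not give either printed figure. With the 2 dropped from the first root it gives both:

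- 3.6% vs 8.9%: p̄ = 0.0625, √(p̄q̄) = 0.24206, √(p₁q₁ + p₂q₂) = 0.34027. n = (0.39815 + 0.28638)² / 0.053² = **166.815** (printed 166.82).
- 3.6% vs 0%: p̄ = 0.018, √(p̄q̄) = 0.13295, √(p₁q₁ + p₂q₂) = 0.18629. n = (0.21868 + 0.15679)² / 0.036² = **108.779** (printed 108.78).

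Other forms were tried for worsening. The unpooled formula (165.6 at 0%) and the fully pooled formula (168.6 at 0%) cannot reach 108.78 for any TWP rate below 3.6%. The arcsine formula (one-sided, 80%) reaches it only at a TWP rate of about 0.05%, and then gives about 246, not 166.82, for the first contrast. Of the forms tried, only the one with the dropped factor fits both figures.

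**2. The correct formula, per group before drop-out.**

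| Contrast | One-sided 0.05, 80% | Two-sided 0.05, 80% |
|---|---|---|
| Worsening 3.6% vs 0% | (0.30927 + 0.15679)²/0.036² = 167.6 → 168 | 213 |
| Worsening 3.6% vs 1.8% (assumed) | 1,002 | 1,272 |
| Improvement 3.6% vs 8.9% | (0.56308 + 0.28638)²/0.053² = 256.9 → 257 | 327 |

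Even the formula with the dropped factor would need 651 per group if TWP halved worsening, so 109 rests wholly on complete abolition.

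**3. Drop-out.** 109/0.8 = 136.25 → 137. 109 × 1.2 = 130.8 → 131. Neither gives 132. In the first calculation, 167/0.85 = 196.5 → 197, while 167 × 1.15 = 192.05, which is where the 192 appears to come from.

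**4. Does 264 suffice at 0% on TWP?** With no TWP events and x placebo events, the uncorrected chi-square is 2nx/(2n − x). At these sample sizes it passes 3.84 once x ≥ 4. The power is therefore P(X ≥ 4) for X ~ Bin(n, 0.036): 55% at n = 109 and 70% at n = 132 with nobody lost. Both fall short of 80%.

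**5. Power of 384 for the worsening rate.** Two-sided uncorrected chi-square, exact enumeration, at 163 per group (192 × 0.85) and at 192 per group. The TWP rates are assumptions, since the protocol gives none.

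| TWP worsening | Power, 163 to 192 per group |
|---|---|
| 0% | 84–92% |
| 0.5% | 53–60% |
| 0.9% (cut by three quarters) | 36–42% |
| 1.8% (halved) | 15–18% |

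Fisher's exact test is lower: with 192 per group, 69% at 0% and 11% at 1.8%.

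**6. Power of 384 for the improvement contrast.** For 3.6% vs 8.9%, the normal approximation gives two-sided power of 52% at 167 per group and 57% at 192. One-sided, it gives 64% and 69%.

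**The case against.** A reader who applies textbook formulas might infer that 108.78 is impossible for any TWP benefit. The document does not support that. It does not print its formula, and the worked result of 166.82 points to one that gives 108.78 exactly at a TWP rate of 0%. The figure has a traceable origin: a wrong formula and an undisclosed assumption. A sponsor who holds that formula could rebut a claim of impossibility at once.

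A reader might also infer that 384 patients have low power for progression in general. That goes too far. If TWP abolished worsening, which is what 108.78 implies, uncorrected chi-square power would be 84–92%. The low figures belong to partial reductions and depend on assumed TWP rates.

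Finally, power for the worsening rate is not power for the planned primary test. That test compares three categories, so improvement and worsening both feed it. How the two rates are reported may also be left to an analysis plan.

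All three objections stand as limits on the point. They do not rescue the printed numbers. The TWP rate is missing, 109 is too few under a correct formula at any rate, the inflation is wrong, and the section rests its conclusion on the result. That the primary test can be driven by improvement is the reason a significant result need not mean delay.

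**Conclusion.** The point holds in this form. The worsening calculation gives 109 per group where a correct calculation with the same quantiles gives at least 168, or 213 with the two-sided test the protocol plans. It reaches 109 only by dropping a factor 2 and taking TWP worsening as 0%. The improvement calculation that sets 384 has the same error: 167 per group where 257 (one-sided) or 327 (two-sided) are needed. The statement that 264 would do for progression is therefore unsupported even in the most favourable case. The 384 are adequate for the worsening rate only if TWP nearly abolishes worsening, and power falls to 15–18% if worsening is halved.

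This rests on three things: reading 3.6% as a proportion of patients; inferring the formula and the 0% rate from a two-decimal match on both printed figures, since neither is printed; and the assumed TWP rates in the power table.

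**What to change.** 1. Delete the 108.78/264 calculation and the sentence that relies on both results. Alternatively, print the assumed TWP worsening rate with the corrected n and drop-out inflation (for 0%: 168 per group one-sided or 213 two-sided, before drop-out).
2. Correct the same formula error in the improvement calculation, make its sidedness and power match the planned analysis, and restate the power that 384 delivers (about 52–57% two-sided for 3.6% vs 8.9% at 167 to 192 per group).
3. State that 384 is not powered for a partial reduction in worsening. Give the power at named TWP rates and label those rates as assumptions.
4. Limit the claim of delayed progression in the Discussion to what is tested. Report worsening and improvement rates separately by group with confidence intervals, so that a result driven by improvement alone is not read as delay.

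The cost is protocol wording and a more modest claim. No patients need to be added for these changes.

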### Statistical Analysis

All statistical tests will be two-sided tests, and a *p* < 0.05 will be considered statistically significant. Quantitative data to calculate the number of cases will be expressed as the mean, median, standard deviation, minimum, and maximum. Qualitative data will list the frequency and percentages. The demography, other baseline characteristics, and efficacy analyses will be analyzed using the full analysis set (FAS), while the per-protocol set (PPS) and the safety analysis will be performed using the safety analysis set (SS).

Quantitative data will be analyzed using the t-test/Wilcoxon rank-sum test, whereas the qualitative data will be analyzed using the X2 test/exact test. The main outcome measures will be analyzed using the X2 test for comparisons between groups, whereas secondary outcome and monitoring measures will be analyzed using the t-test/signed-rank test to compare the groups. The t-test/Wilcoxon rank-sum test will be used to compare the groups. All analyses will be performed using SAS version 9.3.

Three analysis sets will be used for the data analysis. The first is the FAS, which refers to an ideal set of subjects that are as close as possible to the principle of intentionality analysis (including all subjects randomized into the group and treated at least once). If the main variable is missing in any case, the results of the closest observation will be carried forward to substitute the absent test data. We will ensure that the number of participants in each group to be evaluated in the outcome at the end of the study is as consistent as possible before the start of the study. The second dataset is the PPS, consisting of all cases that are following the research plan. This set will consist of the data of participants with good compliance of 80–120% of the prescribed dose. The CRF contains the details of the case, and the main variables can be measured if the baseline variables are not missing, and there is no major violation of the test scheme. The third dataset is the SS, which will consist of the means of all participants who receive at least one treatment after randomization. The demographic, other baseline characteristics, and curative effect analyses, will be performed on the FAS and PPS, while safety will be analyzed using the SS.

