### Randomization and Data Collection

Patients who meet the criteria will be randomized into TWP and placebo groups. Randomized numbers will be generated by the central randomization system (http://www.tcmcec.net/crivrs/) established by the Clinical Evaluation Center of the Chinese Academy of Traditional Chinese Medicine. The randomized numbers will be ordered based on a given sequence, and patients will be divided into two groups according to the randomized numbers. The probability of participants being assigned to each group or center is not fixed but will be adjusted according to certain conditions. The electronic case report form (eCRF) was established by the Clinical Evaluation Center of the Chinese Academy of Traditional Chinese Medicine. All data will be recorded by the investigator in a CRF and eCRF. Furthermore, a unique random allocation is assigned using a system involving double blinding for participants and researchers. Every follow-up will be required to be logged into the central stochastic system by the investigator and into the central random system to obtain a drug number. The same platform will be used to collect information on the participants, random distribution, and assigned drugs to ensure random and blind methods are implemented and the test results are objective, to improve the quality of the clinical trial.

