### Blinding Method

The central randomization system uses a randomly permuted block design, which includes subject screening, randomization, emergency exposure of blindness, designated drug, and drug supply. Blinding of the investigators, participants, statistician, staff in charge of data collection and clinical research associates will be blinded to the group assignments to avoid bias. In order to perform blinding, the placebo is processed into the same appearance, size, color, dosage form, weight, taste, and even smell like the same as the drug (TangWang prescription) in the treatment group. During the study, if participants experience severe adverse events, investigators will carry out an unblinding and perform urgent management accordingly. Statistician and staff in charge of data collection and clinical research associates, will all be third-party staff who did not involve in the design or patient recruitment of this study.

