### Outcome Evaluation

#### Primary Outcome

The primary outcome of the study is the changes in the degree of retinal microaneurysm lesions before and after treatment. This will be determined according to the following scale: none, mild non-proliferative phase, moderate non-proliferative phase, severe non-proliferative phase, and proliferative phase, which are divided into aggravated, unchanged, and reduced conditions. The aggravated state is defined as retinal microaneurysm lesions with a degree of severity > grade 1 after treatment. The unchanged state was defined as a degree of retinal microaneurysm lesions before and after treatment that is unchanged, while the reduced state is defined as a degree of retinal microaneurysm lesions that is reduced by >1 grade after treatment.

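### The primary outcome has three ordered states, but the plan names only a chi-square test: no primary contrast is fixed, and the plain reading is not the two-rate comparison that was sized

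*Protocol article*

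**What the plan says.** Under Primary Outcome, the article grades the retina on a five-level scale from none to proliferative and turns the change into three states, "which are divided into aggravated, unchanged, and reduced conditions". Improvement is narrow: the "reduced state is defined as a degree of retinal microaneurysm lesions that is reduced by >1 grade after treatment".

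Under Statistical Analysis, the comparison is fixed in one clause: "The main outcome measures will be analyzed using the X2 test for comparisons between groups". No table shape, primary category or use of the ordering is given. The same section states "All statistical tests will be two-sided tests".

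Under Sample Size Calculation, two separate comparisons of rates are sized. The first is reduction, 3.6% on placebo vs 8.9% on TWP, and it produces the 384. The second is increase, 3.6% on placebo with no TWP rate given. The basis is "Assuming that α = 0.05 and β = 0.10 according to the one-sided test".

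Study Design states a directional hypothesis: TWP slows progression.

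On allocation, Blinding Method says "The central randomization system uses a randomly permuted block design" (Study Design agrees, and the Abstract gives 1:1), while Randomization and Data Collection says "The probability of participants being assigned to each group or center is not fixed but will be adjusted according to certain conditions".

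**The concern.** The outcome, the sizing and the test do not line up. The outcome has three ordered states. The sizing compares one proportion at a time. The hypothesis is about progression, yet the calculation that sets the sample size is about improvement. The named test does not say which of these it addresses.

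If it is the ordinary chi-square on all three states, two things follow. The test spends a second degree of freedom that the sizing did not allow for. And a significant result says only that the two distributions differ: more improvement, more worsening, or both at once can produce it. A p-value below 0.05 would then not by itself support the claim that the trial is designed to test.

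**Working it through.** **Inputs.** Reduction 3.6% vs 8.9%, 192 per group, and 15% dropout come from Sample Size Calculation; 192 x 0.85 = 163 completers per group. Two-sided 5% comes from Statistical Analysis. Worsening rates are assumed wherever TWP needs one, because the article gives none. Placebo worsening is 3.6%, from the second sizing calculation, unless stated otherwise.

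**The plan's own figure.** The stated n of 166.82 per group does not reproduce. With its quantiles, "uα = 1.64485 and uβ = 0.84162", the unpooled formula gives

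(1.64485 + 0.84162)² x (0.036 x 0.964 + 0.089 x 0.911) / 0.053² = 6.1825 x 0.11578 / 0.002809 = 255.

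The pooled formula gives 258. That is a separate sizing problem. The comparison below uses the planned group sizes and does not depend on it.

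**Two-rate test (1 df).** Power = Φ{[√n x 0.053 − 1.96 x √(2 x 0.0625 x 0.9375)] / √0.11578}.
- n = 163: Φ(0.017) = 51%.
- n = 192: Φ(0.186) = 57% (58% by simulation).

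**2 x 3 chi-square (2 df).** The noncentrality is n x Σ(difference² / sum of the two rates), over the three states.
- Worsening is 3.6% in both arms, so unchanged is 92.8% vs 87.5%.
- Σ = 0.053²/0.125 + 0.053²/1.803 + 0 = 0.02247 + 0.00156 = 0.02403.
- n = 163: noncentrality 3.92, power 41%. n = 192: 4.61, power 47%.

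The 2-df test therefore loses about 10 points at the planned effect.

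**Other scenarios.** Simulation, 40,000 trials each, two-sided 5%. Cells give power at 163 / 192 per group; independent runs agree to about a point. The ordinal test is a tie-corrected rank-sum test.

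| Reduced (placebo, TWP) | Worsened (placebo, TWP) | 2-df chi-square | Ordinal |
|---|---|---|---|
| 3.6%, 8.9% | 3.6%, 3.6% | 41 / 47% | about 33 / 38% |
| 3.6%, 8.9% | 3.6%, 1.8% | 48 / 56% | 59 / 67% |
| 3.6%, 8.9% | 3.6%, 0.9% | 62 / 70% | 72 / 80% |
| 3.6%, 10% | 3.6%, 10% | 88 / 93% | about 5% |

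With more worsening on placebo, at 192 per group and reduction 3.6% vs 8.9%:
- Worsening 10% in both arms: chi-square 48%, two-rate test 58%, ordinal about 25%.
- Worsening 10% vs 5%: chi-square 70%, ordinal 79%.
- Worsening 10% vs 15% (TWP worse): chi-square still significant in 69%, ordinal in 5%.

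**Baseline grade.** Mild, moderate and severe NPDR are all eligible. If improvement needs a fall of more than one grade, a mild eye has only one grade to fall and can never be reduced. If aggravation is read the same way, a severe eye has only one grade to rise and can never be aggravated. A one-grade change then fits no state. So baseline grade determines which outcomes are possible. The simulations do not include it, so they give no figure for the gain from stratifying.

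**The case against.** The strongest reply is that the article never says 2 x 3. The sizing treats reduction and increase separately, which fits 2 x 2 tests at least as well. A 2 x 2 chi-square on reduced vs not is the sized comparison apart from sidedness, and it has a direction. This stands: a reader might infer that the planned test is definitely not the sized one, and the text does not establish that. But the text does not establish the 2 x 2 reading either, and with two directions sized it would still leave open which one is primary.

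Three further inferences should be resisted.
- **That the analysis is unadjusted and ignores centre.** This rests on silence. An article commonly leaves covariates and centre to the analysis plan, which is not shown, and an unadjusted chi-square is valid in a randomised trial. Stratifying by grade is a recommendation here, not an error found.
- **That an ordinal test is simply better.** It is not. Under the only effect stated for both arms, with equal worsening, it is the weakest of the three tests. Its advantage needs TWP to reduce worsening as well, at rates the article does not give.
- **That 88 / 93% is a false-positive rate.** The distributions do differ in that scenario, so rejection is correct; what fails is the inference of benefit. The plan also reports frequencies and percentages, so the mixed movement would be visible.

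The allocation wording is a separate matter and does not show that the chi-square is wrong.

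**Conclusion.** The point holds in this limited form: the article fixes a test without fixing the contrast. On the plain 2 x 3 reading, the test has no direction and does not match the sizing. The cost is about 10 points of power at the planned effect (41 / 47% against 51 / 58%), plus a primary p-value that cannot by itself be read as benefit. The power loss rests on the article's reduction rates and on equal worsening in the two arms; the mixed-movement figures rest on assumed rates. If a 2 x 2 test on reduced was intended, the power loss disappears and what remains is an unstated contrast and the one-sided against two-sided mismatch. This should be corrected before unblinding, but it does not make the analysis invalid.

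**What to change.** In Statistical Analysis:
1. Name one primary contrast.
2. Use a matching 1-df test, two-sided with a sign that shows direction, stratified by baseline NPDR grade. Either use a Cochran-Mantel-Haenszel (CMH) test on reduced vs not, which matches the sizing, or use a CMH row-mean-score test or proportional-odds model across the three states.
3. Give the effect estimate with a 95% CI, and report improved and worsened rates separately.
4. Size the trial for that same two-sided test.

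In Primary Outcome, state how a one-grade change is classified; until then the strata for mild and severe eyes cannot be interpreted.

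Separately, reconcile the statement that allocation probabilities are not fixed with 1:1 permuted blocks. If allocation is adaptive, name its factors and include them in the analysis.

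The cost is wording and standard SAS procedures; baseline grade is already recorded. The real cost lies in the choice of test. The ordinal option gains about 7 to 11 points over the 2-df test if TWP moves both tails favourably. It loses power if only improvement changes: about 33 / 38% with 3.6% worsening in both arms, and about 25% at 192 per group with 10%. The choice must therefore be made before any unblinded data are seen.
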